**For secondary objective 2.2 (Immunogenicity)**

Elderly who have not yet been vaccinated, but have presented to the district hospital for vaccination will be asked by trained study staff at the district hospital to join the immunogenicity subset of the study regardless of whether they joined the primary study. Elderly will be informed of the objective aim, protocol, risks and benefits of joining the immunogenicity study. If elderly consent, they will be asked to have blood drawn before being vaccinated with the inactivated, trivalent influenza IIV3 vaccine the same day (day 0), and return to the district hospital again to have blood drawn 28 days (1 month), 180 days (6 months) and 360 days (1 year) after receiving the vaccine. One additional blood draw will be requested after 28 days of second vaccination in the year 2 to compare the effect of prior vaccination on level of immunological response. For participants unable to travel to the health center, the research nurse will travel to the elderly participant's home and obtain the necessary blood sample, and transport the sample back to the district hospital in ice packs. Participants will be asked for 5cc of blood per scheduled appointment. The serum will be separated from the blood samples using a centrifuge at the district hospital and stored in a refrigerator between 4-8°C for a week or less. On a weekly basis, the serum samples will be transported in ice-packs for less than 24 hours to the NIH laboratory in Nonthaburi. When participants consent to being enrolled, the study staff that consents and enrolls them will also take an electronic baseline assessment questionnaire CRF that should take about 15 minutes to administer. They will provide the participant with a study ID card which has their individual study number and the days of their next scheduled appointments. The card will also have a number to call a study team member if the participant should need to reschedule their appointment or has any other issues or concerns.

Once the serum samples reach the NIH laboratory, hemagglutination inhibition assay (HAI) will be used to measure influenza antibody count specific to the three strains in IIV3: influenza A H1N1, influenza A H3 and influenza B(5). In order to perform this measurement, serum is first diluted and treated to remove nonspecific agglutinins. Red blood cells (RBCs) are mixed with phosphate buffered saline (PBS) solution and standardized to a 0.5% concentration. Chosen influenza strains are used to create standardized control antigens through titration and back titration(5). Specific amounts of serum and antigen controls are eventually mixed in PBS in a microtitre plate and incubated. RBCs are then mixed in and the mixture is set in room temperature until the RBCs in the mixture settle(5). Once the mixture is settled, the antibodies

are counted. Seroconversion will be measured as the percent of participants who have one of the following: a baseline HAI titer of  $<10$  and a post vaccination titer of  $\geq 40$ ; or a baseline HAI titer of  $\geq 10$  and a  $\geq 4$  fold increase post vaccination(6). The results of the serum samples will also be recorded into the centralized database by study staff in Nonthaburi.

## **7.5.2 Participant selection method**

### Primary study

That Phanom and Plapak Districts have approximately 6,000 and 3,000 elderly members, respectively. There are 136 villages in That Phanom and 85 villages in Plapak. In order to maintain population proportions, approximately 2/3 of the 3,500 calculated necessary sample size will be chosen from That Phanom (about 2,333 individuals) and approximately 1/3 will be selected from Plapak (about 1,167 individuals). To get proportional representation, we will use systematic random sampling. The elderly will be sorted in this order: district, sub-district, village, 5-year age band. The sampling interval will be calculated as the total number of elderly residents divided by the total sample size. A random number will be selected from within the sampling interval as the starting point. The random start plus the sampling interval will be applied to the list to select the sample.

### Functional status sub-study

One hundred fifteen elderly with a first ARI or SARI will be interviewed within three to four weeks of the onset of their illness to determine their VES-13 score. A participant who has not had ARI or SARI since the start of the study will be randomly selected from among those who match the case on age ( $\pm 5$  years), sex, influenza vaccination and most recent functional status measurement and interviewed for functional status at the same time as the case.

### Immunogenicity study

All elderly that meet the inclusion and exclusion criteria who come to the district hospital to obtain the influenza vaccine beginning from 15 May, 2015 will be asked to join the immunogenicity study. The first 384 elderly who consent will be enrolled in the study. Consent will be sought again from this group at the start of the second year for additional study to compare the difference in immunologic response after subsequent vaccination.

### **7.5.3 Data collection and tool**

For the community study, health volunteers and study team members will be responsible for collecting baseline data from consented participants during enrollment. Baseline data includes questions regarding health and disease states, education and wealth (Appendix 4B) and also people living with the participant (Appendix 4i, which will be collected after approval of the protocol amendment, once at the subsequent health volunteer weekly follow up). Onwards, trained health volunteers are responsible for collecting all data in the community regarding details of new episodes of ARI/SARI on a weekly basis, functional status of participants 3 to 4 weeks after the onset of the ARI/SARI, and total costs of having an ARI/SARI 1 week after the participant recovers (Appendix 4c, 4d, 4f and 4g, respectively). Trained nurses will be responsible for collecting data on episodes of ARI/SARI for participants who come to their health center for treatment after their appointment (Appendix 4e). Participants will be responsible for collecting nasal self-swabs in the community and trained research nurses will be responsible for collecting nasopharyngeal swabs at health centers. The health volunteers and study team members will be responsible for transporting all nasal specimens to NIH in Nonthaburi for analysis. For the immunogenicity study, a research nurse will be responsible for collecting data during enrollment regarding immunity of the participant and collecting all blood draws (Appendix 4h). The study team will be responsible for transporting the blood samples to NIH in Nonthaburi for analysis. All data collected by health volunteers, the study team and nurses (including enrollment questionnaires, weekly questionnaires, and follow-up questionnaires) will be on electronic CRFs on a hand-held computer device and will be transmitted to a central database system on at least a weekly basis by health volunteers and the study team, and on a daily basis by research nurses. Laboratory results of respiratory swabs and blood samples will be entered onto a separate database at the NIH laboratory in Nonthaburi and linked to the central database later on via the unique assigned identification number.

### **7.6 The process of obtaining informed consent**

For the primary study, written informed consent will be sought from the participant at the participant's home by trained health volunteers, prior to enrollment with the presence of a witness. Study staff will also request written informed consent from village leaders in the

selected sub-district for permission for their village to participate. For the immunogenicity study, written informed consent will be obtained from elderly coming for their influenza vaccination at the district hospitals in That Phanom and Plapak by trained study staff and in the presence of a witness.

For the immunogenicity study, a trained research nurse will meet the vaccination team at both district hospitals during regular business hours and during mobile vaccination clinic runs in the community. When an elderly person approaches the vaccination counter at each hospital or mobile clinic, the research nurse will screen him/her to see if he/she is eligible for the study. If eligible, the nurse will read through the contents of the information sheet disclosing all risks and benefits, answer questions the elderly person may have and ask the elderly person if they would like to enroll into the study. The elderly will also be assured that they may refuse to join the study for any reason without any repercussions and will be able to obtain a vaccination either way. If the elderly person agrees, the nurse will be responsible for consenting and enrolling the elderly into the study. Before take blood draw at the follow up 360 days, nurse will do a new consent elderly person for additional study. If the elderly person refuses for any reason or is ineligible, the nurse will direct the elderly person to the vaccination team who will administer the influenza vaccine to the elderly. In instances in which consenting persons are unable to read, health volunteers and/or study staff will read an oral consent script and then collect written documentation of oral consent for study participation. Consent forms are written in English at the Flesch-Kincaid reading levels of 6.9. All consents will be translated into Thai by an experienced translator and checked by a senior Thai scientist who is fluent in both Thai and English languages. These will then be back-translated to ensure accuracy.

Personnel enrolling individuals into the study will be trained to ensure that potential participants feel no pressure to join the study and understand that enrollment is optional.

The study participants will be clearly notified of the purpose of the study, and what will be required of the participant during the study.

Participants in the study will be notified that there are minimal risks associated with being enrolled in the study.

Participants in the study will be notified that there is no health benefits associated with being enrolled in the study.

Study participants will be allowed to withdraw from the study at any time without or loss of benefits to which they are entitled and notified of such.

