Vaccination: Cohort participants, along with all persons aged 65 years and older in the districts identified by the MOPH for increased IIV3 coverage, will be eligible for influenza vaccination through routine vaccine delivery strategies used by the MOPH. No vaccine will be provided as part of this protocol. The study will be enrolling participants from two districts in Nakhon Phanom, That Phanom and Plapak. According to the Nakhon Phanom Provincial Health Office, the vaccination rate in 2014 was calculated to be 52% and 28% in That Phanom and Plapak, respectively. This VE study will follow a pilot program of the MOPH to increase vaccination among the elderly through a concentrated and focused vaccine campaign in the elderly. This year, due to planned vaccination campaigns, we expect the vaccination rate to be around 50% in both districts. A companion study to this protocol, already underway, will evaluate the coverage achieved by the pilot campaign as well as measure factors associated with receipt of the vaccine in this age group.

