### **7.3 Exclusion Criteria**

For primary objectives exclusion criteria include:

- Elderly with body disabilities that may have impact on self- nasal swab or telephone interview (i.e. elderly with stroke)
- Elderly with history of tumor in the nose or nearby areas
- Elderly with history of bleeding order (i.e. hemophilia)
- Elderly who often gets nosebleeds
- Any elderly with an acute medical condition or illness that could not participate in the study

For secondary objective 2.2 (immunogenicity)

- In addition to the primary objectives' exclusion criteria, any participant who has already been vaccinated with an influenza vaccine in 2015
- Known allergy to influenza vaccine or to egg
- Any participant with any medical condition that could prevent them from having a blood draw

For secondary objective 2.1 (functional status)

- Same as the primary objectives' exclusion criteria

For primary objective 1.3 (COPD exacerbations)

- Same as the primary objectives' exclusion criteria

For secondary objective 2.3 (RSV incidence)

- Same as the primary objectives' exclusion criteria

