| 
If yes to both questions 3 and 5, participant is still eligible; please continue with eligibility questions.
 
If not eligible, thank the elderly for his or her time and let them know they are ineligible for the study.
 |                                                                       |                                                          |  |
| 6. Have you received the influenza vaccine in 2015?                                                                                                                                                                                                  |                                                                       | 1 Yes
2 No                                            |  |
| 
If yes, end the questionnaire and thank elderly for his or her time and let them know they are ineligible for the study.
                                                                                                               |                                                                       |                                                          |  |
| 7. Are you here to receive the influenza vaccine this year?                                                                                                                                                                                          |                                                                       | 1 Yes
2 No
77 Do not know
99 Declined to Answer |  |
| 
If replied with no, do not know, or declined to answer, thank elderly for his or her time and let them know they are ineligible for the study
 
If answered Yes, ask the following questions:
                              |                                                                       |                                                          |  |
| 8. Are you allergic to egg, or do you have any known allergy or negative reaction to the flu vaccine?                                                                                                                                                |                                                                       | 1 Yes
2 No
3 Do not know                           |  |

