|                                                                                                                                                                                                                                                                       |               |
|-----------------------------------------------------------------------------------------------------------------------------------------------------------------------------------------------------------------------------------------------------------------------|---------------|
| 9. Do you have any medical condition that could prevent your full participation in having blood drawn?                                                                                                                                                                | 1 Yes
2 No |
| If replied with yes to either question 8 or 9, thank elderly and let participant know they are not eligible for the immunogenicity part of the study. If answered No to both 8 and 9, please inform participant about immunogenicity study and ask for consent |               |

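### Section 7.6 sends everyone ineligible for the immunogenicity study on to the vaccination team, with no exception or handover for people who have just reported egg allergy, or an allergy or bad reaction to influenza vaccine

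*Protocol*

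**What the plan says.** Section 7.6 places the immunogenicity screening where vaccine is given: "When an elderly person approaches the vaccination counter at each hospital or mobile clinic, the research nurse will screen him/her". Eligible people are told about the study and asked to consent. For the rest there is one sentence and one destination: a person who declines for any reason, or who "is ineligible, the nurse will direct the elderly person to the vaccination team who will administer the influenza vaccine to the elderly".

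Section 7.3 lists among the exclusions for secondary objective 2.2: "Known allergy to influenza vaccine or to egg". The screening form (Appendix 4h) applies this at item 8: "Are you allergic to egg, or do you have any known allergy or negative reaction to the flu vaccine". After a Yes to item 8 or item 9, the form tells staff to "thank elderly and let participant know they are not eligible for the immunogenicity part of the study". It gives no further instruction for that person.

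Section 3.1.4 says of the vaccine supply: "No vaccine will be provided as part of this protocol". Vaccination comes through the Ministry's routine delivery.

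**The concern.** The study asks a vaccine-safety question immediately before a possible dose and records the answer. The next written step for a person who says Yes leads to the team that gives the vaccine, and nothing requires the answer to go with them. If study staff follow the text exactly, a safety-relevant reply can stop at the study form. The person may reasonably suppose that a reply given to a nurse at the counter is known to the vaccinators.

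What is at stake is the safe handling of these individuals. The validity of the trial's results is not in question.

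**Working it through.** No arithmetic applies, and the protocol states no figure on this point to reproduce. The check follows one person through the text.

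1. **Arrival.** The person comes to the vaccination counter and is screened there by the research nurse (section 7.6).
2. **Item 7 of form 4h** asks: "Are you here to receive the influenza vaccine this year". No, do not know, or declining to answer ends the screening as ineligible. Only a Yes goes further: "If answered Yes, ask the following questions". Everyone who reaches item 8 has therefore said they came for a dose.
3. **Item 8** covers egg allergy, known allergy to influenza vaccine, or a negative reaction to it. It is broader than the exclusion in section 7.3, which names known allergy only.
4. **Yes to item 8** makes the person ineligible. The form's only instruction is to thank them and tell them so.
5. **Section 7.6** then applies to every ineligible person without regard to the reason. It directs them to the vaccination team and describes that team as giving the vaccine.
6. **Search for an exception or handover.** Section 7.6 has none and form 4h has none. The risk and ethics text (sections 3.2.3, 8.1 and 8.3) adds none. Nor does the protocol describe or refer to any contraindication check by the vaccination team.

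The written path is therefore: came for a dose, reported an allergy or reaction, declared ineligible, sent to the vaccination team. The number of written steps that tell the team about the answer is 0 in section 7.6 and 0 in form 4h.

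The size of the affected group cannot be worked out. The protocol gives the enrolment target of 384 for this sub-study, but not how many people will be screened to reach it, and it gives no rate of Yes answers to item 8.

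**The case against.** The strongest reply is that the clause about the vaccination team describes that team's job and is not an order. Section 7.6 is about consent. It also assures people that declining the study will not cost them the vaccine, so the sentence most naturally means that non-participants return to the service they came for. Read as an order, it would also vaccinate people who had already been vaccinated in 2015 (item 6) and people who said at item 7 that they had not come for vaccine. That cannot be intended, and it would sit badly with the non-interference principle in section 8.3. In addition, the vaccine is given by the Ministry's routine programme, outside this protocol, and contraindication checks are that programme's business. The person also knows their own history and can tell the vaccinators.

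Much of this stands. A reader might infer that the protocol orders vaccination of allergic people, or causes it. The documents do not support that. The clause allows the descriptive reading, the Ministry's team may make its own checks, and a Yes to item 8 can mean a negative reaction and not an allergy. The protocol also never says that such people should not be vaccinated.

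The missing handover remains. Screening and directing people onward are study procedures, carried out by study staff under this protocol. Whichever way the clause is read, the recorded answer is not passed on.

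**Conclusion.** The point holds as a minor participant-safety wording error. Section 7.6 treats all ineligible people alike, names vaccination as what the receiving team does, and provides no exception or handover for those who answer Yes to item 8.

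The conclusion rests on the text of section 7.6 and form 4h being followed as written. It does not assume that the Ministry's team makes no checks of its own; the protocol is silent on that. No harm is shown, no head-count is claimed, and nothing is said here about whether these people should be vaccinated. Sample size, power and every planned analysis are unaffected.

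**What to change.** Make two small changes.

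- **Section 7.6:** replace the end of the sentence so that a person who declines or is ineligible goes back to the vaccination team *for routine vaccination as appropriate*. This keeps the assurance that not joining the study does not cost anyone the vaccine, and it removes the suggestion that vaccination is the fixed outcome.
- **Section 7.6 and form 4h, item 8:** add *If the answer to item 8 is Yes, the nurse informs the vaccination team before any dose is given; the team decides on vaccination under its own rules.*

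Leaving the decision with the team respects section 8.3. The handover need not depend on separate agreement from the person: section 3.2.5 concerns the custody of stored identifiable study data, and it would be a stretch to apply it to a spoken safety remark to clinical staff at the same counter.

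The cost is one brief spoken handover for each Yes, by a nurse whom section 7.6 already places with the vaccination team. No extra staff, visit or procedure is needed.

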## **7.7 Data Collection**

The baseline data from enrollment will be collected on electronic CRFs by the study team and transcribed to a centralized database on a daily basis. Weekly assessments and all follow-up questionnaires will also be collected by health volunteers on electronic CRFs and the responses will be transmitted to the central database at least once a week at the district hospital. When a participant is admitted to the hospital, a research nurse will look at patient charts to inquire reasons for admit and take a nasopharyngeal swab if applicable. All relevant data collected during hospitalization or clinic visits will also be recorded on electronic CRFs, and transmitted to the central database on a daily basis at the district hospital. Laboratory results of respiratory swabs and blood samples will be entered onto a separate database at the NIH laboratory in Nonthaburi and linked to the central database later on via the unique assigned identification number.

Any edits made to the original record in the hand-held computer will be noted in a separate database with record of the time and date, identification number of the person making changes and the change that was made. Personal identifying data will be kept separate from the study database, linked by a unique study identification number. At the conclusion of the study, after data have been cleaned, the table with personal identifying data will be deleted. For the purposes of study oversight, CDC investigators will have access to personal identifying information during the course of the study, until the study is anonymized. Laboratory results will be entered into a separate database and linked to the central study database via the unique study identification number, and personal identifying data linked to the laboratory results will be deleted.

